#### *Trial conduct*

#### *Recruitment*

The recruitment and selection process will be done according to the aforesaid eligibility criteria. To avoid convenience sampling different documents will be created for advertising and publicizing the PICO project. Social networks, television interviews, newspapers and the collaboration of entities/companies will be the main channels for PICO announcements.

All eligible individuals who contact the study secretariat will go through the same selection process, namely: a telephone based pre–selection stage followed by a face to face interview and completion of the screening questionnaire which will supply information about demographics and symptoms, signs and risk factors for KOA occurrence. Volunteers who, after completing the questionnaire, fulfill the ACR criteria for clinical diagnosis [75] will receive a request for an x-ray examination. The exams will be referred to a rheumatologist who will make the final diagnosis according to ACR radiological criteria. In the case of confirmation of the KOA diagnosis, the subject will be invited to a further interview the purpose of which is detailed explanation of the project, obtaining his/her informed consent and familiarization with both the locale and the equipment which shall be used in the tests.

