## Design/Methods

### Study design

PICO is a single-blinded, randomized controlled trial with 3 months duration. Participants will be randomly assigned to one of two groups: aquatic exercise (AE) and control group (CG). Figure 1 provides a flowchart of PICO design. Researchers and personnel responsible for data collection will be blinded four the group classes. The study protocol was approved by the Ethical Committee of the Faculty of Human Kinetics, Technical University of Lisbon. All participants will be informed about the procedures and potential risks and an informed consent will be obtained from them.

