### Osteoarthritis diagnosis and severity classification

To confirm OA and classify its severity the same X-ray protocol will be used for all subjects. Bilateral, anterior-posterior, weight-bearing knee radiographs will be used to identify OA in the tibiofemoral joint, and sunrise views to identify OA in the patellofemoral compartment. Severity of tibiofemoral OA will be measured using the K-L grading scale [80].

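### As the recruitment section is written, the project is explained and consent obtained only after the screening questionnaire and the study-requested knee x-ray, and only for volunteers with confirmed knee osteoarthritis

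*Protocol article*

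**What the plan says.** The Recruitment section puts every eligible caller through one selection process. A telephone stage is "followed by a face to face interview and completion of the screening questionnaire which will supply information about demographics and symptoms", among other items. Volunteers who then meet the ACR clinical criteria "will receive a request for an x-ray examination". A rheumatologist makes the final diagnosis from the films. The next step is conditional on that diagnosis being confirmed: "the subject will be invited to a further interview the purpose of which is detailed explanation of the project, obtaining his/her informed consent", together with familiarisation with the test site and equipment.

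Consent is mentioned in one other place, under Study design: "All participants will be informed about the procedures and potential risks and an informed consent will be obtained from them". That sentence gives no timing.

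On the x-ray, the section on diagnosis and severity classification says: "To confirm OA and classify its severity the same X-ray protocol will be used for all subjects". It specifies bilateral weight-bearing films and sunrise views. Table 2 lists the knee x-ray and the KOPS questionnaire under Recruitment and marks both at Screening.

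**The concern.** Consent should come before the procedures it covers. Here two screening procedures precede it. One is a questionnaire that, with its medical form, collects health and socio-economic data. The other is a set of radiographs that the study asks for in order to decide eligibility. If the order is followed as printed, a volunteer is x-rayed for the trial before hearing the procedures and risks that Study design promises to explain.

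The order matters most for volunteers whose disease is not confirmed. They have answered the questionnaire and been x-rayed, and their path ends before the only consent step described. The article also hopes that later studies will reproduce the protocol, so the sequence could be copied.

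**Working it through.** No calculation applies, because the point depends on the order of procedures and not on any rate, effect or sample size. The check is to line up the sections.

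1. **Order of steps (Recruitment).** Telephone pre-selection; face-to-face interview and screening questionnaire; x-ray request if the ACR clinical criteria are met; rheumatologist's diagnosis; and, if confirmed, a further interview for explanation and consent. The last step depends on the result of the one before it, so it cannot take place before the x-ray.

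2. **Is the questionnaire a trial procedure?** Under Screening measurements, KOPS is the authors' own instrument. Screening records symptoms, risk factors, co-morbid diseases, medication, occupation, income and education. Table 2 marks KOPS at Screening and again at 3 months, with no mark at Baseline. The screening KOPS is therefore the only value before the intervention against which the 3-month KOPS can be set. It is trial data as well as a recruitment filter.

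3. **Is the x-ray a trial procedure?** The selection process generates the request, the films follow one specification for all subjects, they serve both to confirm and to grade the disease, and Table 2 schedules them at Screening. The Discussion says that the radiographs are the one measure not obtained in the study's own facility. That concerns where they are taken, not who asks for them or why. (The views are not described consistently: Table 2 names lateral and antero-posterior films, while the diagnosis section names antero-posterior and sunrise views. The consent point does not depend on which is right.)

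4. **Does the Study design sentence cure the order?** It promises information on procedures and risks to participants, without saying when. It can be met for people who enrol, since they consent at the further interview. It does not move that interview ahead of the questionnaire or the x-ray, and it gives nothing to a volunteer who is x-rayed and not confirmed.

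5. **Who is affected?** Everyone sent for x-ray: all who are later randomised (50 in the Abstract, 56 under Inclusion criteria) and all who are x-rayed and not confirmed. The second number is not given and cannot be derived from the article.

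Read together, the sections place both the data collection and the radiographs before the only consent step that is given a time.

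**The case against.** The strongest reply is that the article does not say that nothing is agreed earlier. A detailed explanation at the later interview is compatible with a shorter one by telephone or at the first interview. A journal article condenses a full protocol, consent forms were removed from the text reviewed, and the ethics committee approved the study. This stands in part: a separate screening consent cannot be excluded. It does not dispose of the point, because the article does more than stay silent. It states an order, and puts the detailed explanation of the project after the x-ray.

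A second reply is that the x-ray may be useful diagnosis for people with symptoms who already meet clinical criteria and whose films a rheumatologist reads. That is fair, and the exposure should not be described as purely research radiation. But the films are requested to settle trial eligibility under a common study specification, so they still belong among the procedures to be explained beforehand.

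A third reply is that Study design speaks of participants while Recruitment speaks of volunteers and subjects, so there is no strict contradiction. That is correct as a matter of wording. The gap remains that the article states no consent for the screening procedures.

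A reader might go further in three ways that the article does not support:

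- **That volunteers definitely undergo screening without any agreement.** The text shows only that no earlier agreement is described.
- **That data on screen failures cannot be kept or counted in the flowchart.** Nothing in the article says that their individual data will be retained or analysed, the figure is not shown, and a flowchart ordinarily needs only counts.
- **That a definite number of people are x-rayed without consent.** No radiographic failure rate is given, and refusals and other exclusions after confirmation are also unknown, so any figure would be invented.

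**Conclusion.** The point holds as a matter of stated order. The Recruitment section places the detailed explanation and the only timed consent step after the questionnaire and the study-requested x-ray, and restricts that step to volunteers with confirmed disease. It reaches everyone sent for x-ray; the total is unknown.

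This is a matter of protecting volunteers and of clear conduct. Sample size, power, the significance level and the randomised comparison are unaffected. No radiation dose is given, so the case rests on the sequence and not on the size of any harm. The conclusion assumes that the article reports the actual sequence. If a screening consent is already taken at or before the face-to-face interview, what remains is an error of description in the Recruitment section.

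**What to change.** At the existing face-to-face interview, before KOPS and the x-ray request, explain the project and obtain consent, or obtain a short screening consent covering the questionnaire, the x-ray and the use of screening data. Keep the interview after diagnosis for full trial consent, or for confirmation and familiarisation.

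If a screening consent already exists, correct the order in the Recruitment section and add to the Study design sentence when each consent is taken, so that the two agree.

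The cost is a reordered paragraph and, where none exists, a short screening form submitted to the ethics committee. No visit, measurement or analysis is added.

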### Intervention programs

#### *Aquatic exercise (AE)*

The aquatic program is based on the guidelines of OARSI and EULAR for KOA management [28,29], on the Aquatic Exercise Association Guidelines (AEA) [72], on the Arthritis Foundation Aquatics Program instructor’s manual [73], on the ACSM’s Guidelines for Exercise Prescription [76] and on analysis of the protocols of previous studies [36,38,39,44,77,78].

The strategies in the PICO proposal to produce a high quality aquatic exercise intervention are structured according to AEA guidelines [72] and include overload assessment and managements, impact level control (level 1, 2 or 3), exercise cadence control and adequate music according to exercise goals. In addition the use of different and pre-defined cool-down sessions each week, a strong motivational component and pain assessment should make the difference in this protocol. Educational themes shall also be addressed during the classes. One educational theme per week shall be reinforced, such as: *What did you have for breakfast? Let’s try, during this week, to improve the quality of our breakfast. Next class I will check what you ate; remember that you should assess yourself about knee pain, let’s try to learn how to live with it.*

Another aspect that will be considered is the level of aquatic ability of each participant. Exercises like underwater breathing and flotation will be used in small doses to reduce fear of water and to ensure that participants are comfortable moving around the pool.

The aquatic program will be organized into 24 sessions distributed over 12 consecutive weeks, with a frequency of twice a week. The duration of each session will be 60 minutes, being that 10 minutes are for patient reception, blood pressure control, pain registry etc., and the effective time inside the water is 45 minutes. The indoor pool works with an air temperature around 27 ± 1°C and water temperature is controlled at 30.5 ± 0.5°C.

Table 1 describes the aquatic exercise class format for the first four weeks. Workouts are organized in order to have a progressive overload every week. Water is the main instrument to create resistance and only in the last week, according to the level of progression of the participants and whether their self-reported pain is controlled, will additional equipment be added to increase the water resistance and consequently, the exercise overload. The Omni - Perceived Exertion Scale for Resistance Exercise (OMNI-RES) and for aerobic target zone (0–10 Borg Scale) will be used according guidelines for exercise intensity management [76].

**Table 1 T1:** The aquatic exercise protocol design for the first 4 weeks of the PICO program

**Music BPM**	**Week1-5 (128 bpm)**	**Week 1**	**Week 2**	**Week 3**	**Week 4**
**Warm up **(5-8′)	**Duration**	8′	8′	8′	8′
	**Patterns**	Walking combined with static and gentle movements of main joints. Use hands to keep thermal comfort	Walking combined with static and gentle movements of main joints	Walking combined with static and gentle movements of main joints	Walking combined with static and gentle movements of main joints
**Aquatic adaptation**		Vertical balance	Vertical balance	Submersion	Submersion
		Travellings	Travellings	Underwater breathing	Underwater breathing
**Aerobic** (15-30′)	**Duration**	3x5min	4x5′	4x5′	(1x10′) + 5′ + 5′
	**Exercise pattern**	Walking patterns with variation of upper limb patterns	Walking patterns with variation of upper limb patterns	Walking patterns with variation of upper limb patterns	10′ walking patterns + (2x5′) de basic aquatic patterns (Jumping jack, Ski, Leg Curl and Kicks)
	**Intensity (%HRmax and RPE scale)**	57%-67% RPE 4-6	57%-67% RPE 4-6	57%-67% RPE 4-6	64-74% RPE 5-6
	**Impact level**	1	1	1	1
**Strength**	**Repetitions**	2x8	1 x16	2x16	2x16^t1^ + 1x8^tt^
	**Cadence**	t1 = water tempo	t1 = water tempo	t1 = water tempo	t1 = water tempo tt = land tempo
	**Sets interval**	Active 1-2′	Active 1-2′	Active 1-2′	Active 1-2′
	**Equipment added**	No	No	No	No
	**Intensity (Omni-RES)**	6-7	6-7	6-7	6-7
**Cool down **(5-6′)		Static stretching on the wall	Static stretching (center)	Dynamic/static stretching (center)	Dance + Dynamic/static

RPE- Rate of perceived exertion scale.

The exercise instructors will use behavioral techniques: 1) to encourage social contact between participants; 2) to promote frequent contact during all intervention phases; 3) to define clear behavioral goals and allow feedback on achievements; 4) to help participants to self-monitor their pain and exercise intensity to complete activity; 5) to establish personal commitment to the project through the exercise leader.

#### *Educational program: control group (CG)*

The control group will not be enrolled in any exercise program but will participate in the educational program “PESO comunitário”. This program is based on appropriate clinical guidelines and on validated behavior change principles [79]. Implemented by an intervention team with expertise gained from current scientific research in weight control determinants, this program, as is PICO, is free of charge for all interested adults who wish to manage their weight and health. It has operated since 2005 with the objective of preventing obesity or reducing excess weight as well as some of the risk factors for adult obesity, via through a change to steady healthy habits, attitudes and behaviors. PESO lasts 3 months and comprises 12 sessions of one and a half hour, on a weekly basis.

### Measurements

#### *Screening measurements*

The **Knee Osteoarthritis Pre-Screening questionnaire** (KOPS) was validated by the authors and considered useful for this purpose (article in submission process). KOPS addresses physical function, activity level, co-morbid diseases, KOA risk factors and symptoms, height and weight (to determine BMI) as well as caregiver status. The demographic data that are collected include data on occupation, income, and educational level. The medical form is used to determine co-morbidities and to analyze any self-reported information on medications. The overall KOPS score has acceptable to good reliability with a Cronbach’s Alpha of 0.747 and satisfactory internal consistency with an Intraclass Coefficient (ICC) for average measures of 0.646. The results for test-retest of one-week interval for each component ranged from 0.895-0.992 for ICC and from 0.894 to 0.979 for Cronbach’s Alpha.

### Osteoarthritis diagnosis and severity classification

To confirm OA and classify its severity the same X-ray protocol will be used for all subjects. Bilateral, anterior-posterior, weight-bearing knee radiographs will be used to identify OA in the tibiofemoral joint, and sunrise views to identify OA in the patellofemoral compartment. Severity of tibiofemoral OA will be measured using the K-L grading scale [80].

#### *Outcomes, measures and instruments*

All tests will be performed by all subjects at both baseline and 3 month later, at the end of the exercise intervention, using the same protocols and evaluated by the PICO team member(s). Tests list can be checked in the Table 2. The tests and questionnaires will be distributed over two nonconsecutive days, taking the fatigue levels of the subject and the need to avoid overload into account. Therefore the knee strength test and the Six Minute Walking Test will be conducted on different days.

**Table 2 T2:** Tests list

**ASSESSMENT (TEST)**	**Screening**	**Baseline**	**3 months**
**Recruitment**			
Interview	x		
KOPS	x		x
Knee X-ray (lateral and antero-posterior)	x		
**KOA symptoms and quality of life (Self-reported questionnaires)**			
Pain assessment (Brief pain inventory)		x	x
Knee osteoarthritis associated quality of life (KOOS)		x	x
MOS (SF-12v2)		x	x
Depression assessment (Beck depression inventory)		x	x
Weight and lifestyle inventory		x	x
**Physical function and gait**			
Aerobic capacity (6MWT)		x	x
Strength		x	x
Functional (FRSTS)		x	x
Knee (BIODEX dynamometer)		x	x
Hand (grip dynamometer)		x	x
Flexibility (CRS and BS tests)		x	x
Gait Analysis (Kinematics and kinetics)		x	x
**Morphology and body composition**			
Morphological measures (Anthropometry)		x	x
Body composition (DXA scan)		x	x
**Life style**			
Physical activity level (IPAQ)		x	x
**Inflammation biomarkers**			
Cytokines (blood drawn)		x	x

The main outcomes will be KOA symptoms (pain and stiffness) and quality of life, physical function (aerobic capacity, strength, and flexibility) and gait (kinetics and kinematics). The secondary outcomes are body composition, morphology, physical activity level, and inflammatory biomarkers. During the study, all participants will be allowed to maintain their usual medication, including analgesics and NSAIDs. A detailed record of medication will be done at baseline and 3 month post-intervention testing.

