#### *Sample*

Considering the calculation of the sample size, the studies of Messier (2009) [74] and Wang (2007) [44] were used as a reference, because they had a sample with similar characteristics and studied similar outcomes. Both showed that a reduction of symptoms in patients with OA of the knee led to a significant improvement (α < 0.05) of the primary outcome measure of self-reported physical function. To find an analogous improvement of self-reported physical function of approximately 25% between the baseline and final measurements in patients with KOA, the minimum number of patients that are required is 20 for the main outcomes. The latter number is based on a power (1-B) of 0.80 and a significance level of 5% (two-sided). When a dropout rate of 20% is taken into account, at least 25 participants must be involved at study onset.

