### Inflammatory biomarkers

Our primary measures are IL-6 and IL-10. These cytokines are consistently implicated in OA pathogenesis and showed significant improvement with weight loss in ADAPT. We will also measure hsCRP as an overall marker of chronic inflammation and TNFα and TNFα soluble receptor 1 (sTNFR1) because they are also implicated in OA pathogenesis. Leptin, an adipokine that increases synthesis of TGFβ, a known stimulator of osteophyte formation, will also be measured.

For assessing IL-6, IL-10, hsCRP, TNFα, sTNFαR1 and leptin, venous blood samples (approximately 10 ml per visit) will be collected into dry tubes and EDTA tubes by standard procedures in the morning after a minimum of 4 h fast without any type of exercise.

Blood will be centrifuged at 1500 x g for 10 min to separate serum from the cloth in the dry tubes and plasma from red blood cells in the EDTA tubes. Serum and plasma will be frozen at 80°C for posterior analysis by ELISA using commercially available kits.

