### Statistical analysis

Descriptive statistics, including frequencies for categorical variables and means with standard deviations (SD) for continuous variables with normal distribution and median for skewed distributions will be used to describe subject’s characteristics. Normality will be tested using the Kolmogorov-Smirnov test. For continuous outcome measures, differences in mean change (baseline minus post-intervention) will be compared between groups using analysis of covariance adjusted for baseline values of the outcome. Comparisons between groups (CG and AEG) at baseline and post intervention will be conducted by Independent-sample t-tests or Mann–Whitney U test if equal variance is not assumed. Changes within group will be analyzed by paired Student’s t tests or by the Wilcoxon Signed Rank test when normality is not assumed. A mixed model analyses of covariance (ANCOVAs) will be conducted for interaction analyses adjusted for BMI with two within-participant factors of 6MWT (baseline) and 6MWT (post-intervention) and between two groups (CG and AE). Statistical analysis will be performed using IBM SPSS Statistics 20.0 and MedCalc Statistical Software (MedCalc Software, Mariakerke, Belgium). Multiple Linear regression analyses will be performed to understand the potential covariates that could improve the explanation of the variability of outcomes (6MWT, strength and KOOS dimensions). Statistical significance will be set at P *<* 0.05 (2- tailed) for all analyses. Effect sizes will be calculated for all measures with an effect size of 0.2 considered small, 0.5 medium and 0.8 large.

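### Three whole domains are main outcomes with no single primary variable, every test is at two-sided 0.05, and the function measure behind the sample size is not singled out

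*Protocol article*

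**What the plan says.** **Outcome tiers.** The paragraph after Table 2 (Outcomes, measures and instruments) reads: "The main outcomes will be KOA symptoms (pain and stiffness) and quality of life, physical function (aerobic capacity, strength, and flexibility) and gait". Body composition, morphology, activity level and biomarkers are secondary. No variable, instrument or time point is set above the others in the main tier.

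**Tests.** For continuous outcomes, the Statistical analysis section says that "differences in mean change (baseline minus post-intervention) will be compared between groups using analysis of covariance adjusted for baseline values of the outcome". It also plans between-group comparisons at each visit, within-group tests, a mixed-model interaction analysis of the 6MWT, and regressions for the 6MWT, strength and the KOOS dimensions. The threshold is common to all: "Statistical significance will be set at P *<* 0.05 (2- tailed) for all analyses".

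**Sample size.** The Sample section cites two reference studies with a "primary outcome measure of self-reported physical function". It then sizes this trial to find "an analogous improvement of self-reported physical function of approximately 25% between the baseline and final measurements" and concludes that "the minimum number of patients that are required is 20 for the main outcomes".

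**Where self-reported function sits.** Table 2 lists the KOOS in the self-reported block on symptoms and quality of life. Its ADL and Sport/Rec scales measure self-reported function.

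**Biomarkers.** That section says: "Our primary measures are IL-6 and IL-10".

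**The concern.** A main tier made of domains leaves open which result decides whether the programme worked. With a 0.05 threshold for each variable, the chance of some positive main result by luck grows with the number of variables, and nothing in the text stops that result from being presented as the trial's finding. The Conclusions expect the results to support evidence-based treatment recommendations, which is a confirmatory use.

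The power statement has a related weakness. It was made for one construct, self-reported physical function, but is extended to the main outcomes in general. The outcome list then describes physical function by performance domains. A reader cannot tell which variable the 80% power belongs to. A later report could single out a KOOS scale because of the sizing, or the 6MWT because of its dedicated analysis, and cite this article either way.

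**Working it through.** **1. The plan's own figure.** 20 / (1 − 0.20) = 25, which reproduces the stated minimum after dropout. The 20 itself cannot be reproduced, because no standard deviation or baseline mean is given and the text does not say whether 20 is per group. If it is per group, the implied standardized difference is d = (1.960 + 0.842) × √(2/20) = 0.886 (normal approximation). This is used only in step 5.

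**2. Counting the main variables.** The article gives no number, so I counted the measures it names in two ways.

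| Measure | Sparing | Full |
|---|---|---|
| BPI | 1 | 2 |
| KOOS | 1 | 5 |
| SF-12 | 2 | 2 |
| BDI | 0 | 1 |
| 6MWT (distance, speed) | 1 | 2 |
| Chair sit and reach | 1 | 2 |
| Back scratch | 1 | 2 |
| Five-repetition sit-to-stand | 1 | 1 |
| Isokinetic knee strength | 2 | 4 |
| Isometric knee strength | 1 | 2 |
| Handgrip | 1 | 2 |
| Gait speed | 1 | 1 |
| Gait cycle | 7 | 8 |
| Ground reaction forces | 3 | 9 |
| Moments and angular impulse | 5 | 5 |
| **Total** | **28** | **48** |

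The full count treats sides, subscales and force components separately. The sparing count merges most of them.

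**3. Chance of at least one significant main result when there is no effect on any.** For k independent tests it is 1 − 0.95^k:
- k = 28: 1 − 0.95^28 = 0.76
- k = 48: 1 − 0.95^48 = 0.91

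For k test statistics with common correlation ρ and c = 1.96, it is 1 − ∫ [Φ((c − √ρ·u)/√(1−ρ)) − Φ((−c − √ρ·u)/√(1−ρ))]^k φ(u) du:

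| ρ (assumed) | k = 28 | k = 48 |
|---|---|---|
| 0 | 0.76 | 0.91 |
| 0.3 | 0.64 | 0.80 |
| 0.5 | 0.49 | 0.61 |
| 0.7 | 0.33 | 0.40 |
| 0.9 | 0.17 | 0.19 |

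The expected number of false-positive main results does not depend on correlation: 28 × 0.05 = 1.4 and 48 × 0.05 = 2.4. Even one test per domain (k = 3, independent) gives 1 − 0.95³ = 0.14. All these figures allow one test per variable. The visit-wise, within-group and regression tests would add more.

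**4. Construct used for sizing against construct listed.** The Sample section uses self-reported physical function. The outcome list uses aerobic capacity, strength and flexibility, which Table 2 and the Physical function and Strength sections assess by the 6MWT, sit-to-stand, dynamometry, chair sit and reach, and back scratch. These are performance tests. The self-reported function scales come in through the KOOS, under symptoms and quality of life.

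**5. What each remedy does to power (assuming 20 per arm and d = 0.886).**

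| Remedy | Alpha per test | Power | Needed per arm |
|---|---|---|---|
| One primary | 0.05 | 80% | 20 |
| Bonferroni, 3 domains | 0.0167 | 66% | 27 |
| Bonferroni, 28 variables | 0.0018 | 37% | 41 |
| Bonferroni, 48 variables | 0.0010 | 32% | 44 |

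**The case against.** A reader might infer that the outcome used for sizing is missing from the main outcomes altogether. The documents do not support that. The KOOS, with ADL and Sport/Rec, sits in a main domain, the Statistical analysis section names the KOOS dimensions as outcomes, and the Sample section ties its number to the main outcomes. What is missing is any sign that these scales come first.

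The article does have a hierarchy, since it separates main from secondary outcomes. A detailed multiplicity procedure is also commonly left to a statistical analysis plan. Both points are fair. The gap, however, is inside the main tier, and the article does not stay silent there: it sets one threshold "2- tailed) for all analyses".

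The count is mine, and it contains redundancy. 6MWT speed is distance over a fixed time, for example, and related gait variables move together. Independence is therefore implausible and 91% is an upper figure. It would go too far to say that a false-positive main result is more likely than not: at a correlation of 0.7 the chance is 33% to 40%.

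The phrase calling self-reported function primary describes the reference studies and does not designate an endpoint for this trial. The IL-6 and IL-10 sentence might be read as a second primary outcome. In its section, where further markers follow as additional measurements, it most naturally ranks markers within the panel, so it needs only a wording edit.

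**Conclusion.** The point holds in this form. The main tier contains many variables and no designated primary, all tested at two-sided 0.05. The chance of at least one false-positive main result is about 33% to 91%. The range rests on a count of 28 to 48 and a common correlation from 0.7 down to 0; at 0.5 it is 49% to 61%. Even at a correlation of 0.9 it stays more than three times the nominal 5%.

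The sample size section and the outcome list describe physical function differently, so the stated power is not tied to an identified variable. The Sample section names no instrument for the 25% improvement. KOOS ADL is therefore the closest candidate and not the documented sizing outcome; Sport/Rec or the SF-12 physical component could also be meant. This should be settled before any between-group result is seen.

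**What to change.** - Name one primary endpoint that matches the construct in the Sample section. An example is the KOOS ADL score at 3 months, aquatic exercise against control, by the planned baseline-adjusted ANCOVA at two-sided 0.05.
- State the same variable in the Sample section and in the outcome list, and say there whether physical function means self-report or performance.
- Make the other main outcomes secondary or exploratory. Report them with estimates and 95% confidence intervals, or apply Holm within each domain. Holm by domain does not control error across domains, so it supplements the single primary and does not replace it.
- In the biomarker section, say that IL-6 and IL-10 are the main biomarkers among the secondary outcomes.

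The cost is wording in four sections, with no new measurements or participants. The real price is that pain, gait and performance results lose confirmatory status. Keeping several primaries with correction would cost more: under the assumptions above, Bonferroni over the three domains alone lowers power from 80% to 66%.
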